### End of Study Definition

The definition of the end of the study is the point at which the last patient recruited has had the last visit at the end of the 1-year follow-up session.

### Participant Withdrawal

#### Overview

A patient may withdraw, or be withdrawn, from trial treatment for the following reasons:

1. If the patient has to undergo urinary catheterization for relieving blockage symptoms while undergoing EBRT and should not proceed further with HDR.

2. Any other unforeseen toxicity developed during RT treatment, and as a consequence the patient is unable to finish the protocol treatment.

The withdrawn patients will be followed as per protocol up to the end of year 1 from the time of completed treatment. With ongoing consent, patients should remain in the trial and be followed up according to the protocol visit schedule.

#### Withdrawal of Consent

Patients may withdraw their consent to participate in the trial at any time. If the patient explicitly states their wish not to contribute further data to the study, the investigator should inform the coordinating center in writing and the withdrawal of consent should be documented by the investigator in the patient’s case report form (CRF). However, data up to the time of consent withdrawal will be included in the data reported for the study.

Although the participant is not obliged to give the reason for withdrawing their consent, this information will help ascertain any trends related to trial procedures and may influence the protocol development in future projects.

### Laboratory Tests

All laboratory tests will be taken as per the standard of care within the local pathology department at Southend University Hospital National Health Service (NHS) Foundation Trust. Tests include full blood count (FBC), liver function tests (LFTs), urea, electrolytes, and PSA.

The samples will be collected by the trial nurse, labelled and logged in the CRFs, processed according to the local standard operating procedures (SOPs), and the results will be recorded in the CRFs.

### Pharmacovigilance

#### General Definitions

##### Adverse Event

An adverse event (AE) is any untoward medical occurrence in a participant to whom a medicinal product has been administered, including occurrences which are not necessarily caused by, or related to, that product. An AE can, therefore, be any unfavorable and unintended sign, including an abnormal laboratory finding, symptom, or disease temporarily associated with study activities.

##### Serious Adverse Event

A serious adverse event (SAE) fulfils at least one of the following criteria: (1) is fatal—results in death (NOTE: death is an outcome, not an event), (2) is life-threatening, (3) requires inpatient hospitalization or prolongation of existing hospitalization, (4) results in persistent or significant disability/incapacity, (5) is a congenital anomaly/birth defect, or (6) is otherwise considered medically significant by the investigator.

#### Investigator’s Assessment

##### Seriousness

The chief investigator (CI) or principal investigator (PI) responsible for the care of the participant, or in his absence an authorized medic within the research team, is responsible for assessing whether an event is serious according to the definitions given above.

##### Causality

The investigator must assess the causality of all serious adverse events in relation to the trial treatment according to the definitions given above.

##### Expectedness

The investigator must assess the expectedness of all SAEs according to the definitions given above. If the SAE is unexpected and related, then it needs immediate reporting.

##### Severity

The investigator must assess the severity of the event according to the following terms and assessments. The intensity of an event should not be confused with the term “serious” which is a regulatory definition based on participant/event outcome criteria.

1. Mild: intensity of an event is mild if some discomfort is noted, but without disruption of daily life.

2. Moderate: intensity of an event is moderate if discomfort is enough to affect/reduce normal activity.

3. Severe: intensity of an event is severe if it causes a complete inability to perform daily activities and lead a normal life.

####  Notification and Reporting of Adverse Events or Reactions

If the AE is not defined as *serious*, the AE is to be recorded in the study file and the participant is to be followed up by the research team. The AE is to be documented in the participant’s medical notes where appropriate, and in the CRF.

####  Notification and Reporting of Serious Adverse Events

Serious adverse events that are considered to be *related* and *unexpected* are to be reported to the sponsor within 24 hours of learning of the event and to the main research ethics committee (REC) within 15 days in line with the required time frame. For further guidance on this matter, please refer to Multimedia Appendix 1.

#### Urgent Safety Measures

The CI may take urgent safety measures to ensure the safety and protection of the clinical trial participants from any immediate hazard to their health and safety, in accordance with Regulation 30 of The Medicines for Human Use (Clinical Trials) Regulations 2004: SI 2004/1031. The measures should be taken immediately. In this instance, the approval from the licensing authority prior to implementing these safety measures is not required. However, it is the responsibility of the CI to inform the sponsor and main research ethics committee—via telephone—of this event immediately.

The CI has an obligation to inform the main ethics committee *in writing within 3 days*, in the form of a substantial amendment. The sponsor must be sent a copy of the correspondence with regard to this matter. For further guidance on this matter, please refer to Multimedia Appendix 1.

#### Annual Safety Reporting

The CI will send the Annual Safety Report (ASR) to the main REC using the National Research Ethics Service (NRES) template—the anniversary date is the date on the multicenter research ethics committee (MREC) “favorable opinion” letter—and to the sponsor.

####  Overview of the Safety Reporting Process/Pharmacovigilance Responsibilities

The CI has the overall pharmacovigilance oversight responsibility. The CI has a duty to ensure that pharmacovigilance monitoring and reporting is conducted in accordance with the sponsor’s requirements.

### Statistical Considerations

#### Primary Endpoint Analysis

Percentages will be compared using Fisher’s exact test. This analysis will be carried out after the end of the follow-up at 12 months.

#### Secondary Endpoint Efficacy Analysis

For the IPSS and IIEFS scale scores, the two means at each of the follow-up assessments will be compared using a two-sided permutation *t* test, and the 95% confidence limits for the difference between the means will be calculated using a bootstrap method. There will also be an assessment of trends in the scores over time using a repeated measures analysis of variance on the four follow-up scores, with the baseline score as a covariate. Prostate-specific antigen relapse-free survival will be estimated using the Kaplan-Meier method, with a test for the difference between the survival curves using the log-rank test. Cox proportional hazards multiple regression will also be used to assess the effects of covariates on survival. For this feasibility study, this analysis will be carried out after the end of the follow-up at 12 months, whereas for a main study a longer follow-up period would be considered.

#### Safety Endpoints

As the primary endpoint is concerned with adverse events, this will be a central concern of the primary endpoint analysis as described above—the analyses will be carried out after the end of the follow-up at 12 months.

#### Sample Size

In this feasibility study, the sample size has not been determined according to statistical principles, but is the number judged to be suitable for evaluating the suitability of the processes and procedures of running the study, and for assessing the patient experience and adherence in the study. To this end, two samples of 25 patients—50 overall—will be randomized to the two treatments.

#### Statistical Analysis

Although the sample size will be small, there will nevertheless be attempts to analyze the data in the same way as would be the case for a main study. However, this might not always be possible depending on the pattern of the outcomes and missing values. For descriptive statistical summaries, continuous data will be summarized using means, medians, standard deviations, interquartile ranges, and ranges. Categorical data will be summarized using counts and percentages. All statistical significance testing will be at the 5% significance level. For the IPSS and IIEFS scale scores, the two means at each of the follow-up assessments will be compared using a two-sided permutation *t* test using 1,000,000 random permutations, and the 95% confidence limits for the difference between the means will be calculated using a bootstrap method using 9999 resamplings. There will also be an assessment of trends in the scores over time using a repeated measures analysis of variance on the four follow-up scores with the baseline score as a covariate.

For categorical data based on adverse events, percentages will be compared using Fisher’s exact test. In this small study it will be possible to carry out the full combinatorial calculations for Fisher’s exact test, whereas in a main study, 10,000 random permutations will be obtained in a Monte Carlo approach. For differences between percentages, the 95% confidence limits will be obtained using Newcombe’s Hybrid Score Interval method. For the secondary analysis, prostate-specific antigen relapse-free survival will be estimated using the Kaplan-Meier method, with a test for the difference between the survival curves using the log-rank test—the *P* value will be obtained using a permutation test with 10,000 permutations. Cox proportional hazards multiple regression will also be used to assess the effects of covariates on survival, with model comparisons carried out using likelihood ratio tests. The analyses will be performed using the computer program R. All randomized participants will be included in the analyses. There are no planned interim analyses.

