This randomized feasibility study will look at the treatment arms according to the timing of HDR brachytherapy—either before or after EBRT—and their toxicity profiles. The study is called Timing of HDR brachytherapy with EBRT in Prostate CAncer (THEPCA). Assessment of acute and late toxicities and other parameters in these two arms at various time points will enable appropriate sequencing of EBRT and HDR therapy resulting in an optimal level of reduced toxicity. The treatments from both arms will be delivered with standard planning techniques. The incidence of grade 3 genitourinary toxicity is 1.6% in this cohort of patients [5]. Additionally, this feasibility study will also explore the challenges of image-guided radiotherapy planning between the two study arms. Provided a significant difference between the two treatment arms is achieved following final analysis, consideration will be made to use this to inform the development of a further pivotal study to look more deeply into the toxicity and other parameters related to the treatment.

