### Androgen Deprivation Therapy

Patients will receive neoadjuvant and adjuvant antiandrogen therapy from 6 months to 3 years according to the risk stratification of the disease as per the standard of care.

Table 2 shows the schedule of assessments throughout the study.

**Table 2 table2:** Schedule of assessments during the study.

Steps and assessments	Pretreatment time points	Treatment time points		Posttreatment time points^a^				
	Screening^b^and consent	Baseline	Start of second treatment^c^	6 weeks	3 months	6 months	9 months	12 months
Informed consent	*							
Physical examination		*	*	*	*	*	*	*
Vital signs		*	*	*	*	*	*	*
QoL, IPSS, IIEFS, FACT-P, CTCAE^d^		*			*		*	*
Hematology		*						*
Biochemistry		*						*
Concomitant treatment (eg, ADT^d^)		*	*	*	*	*	*	*
Tumor staging	*							
Histological confirmation of diagnosis	*							
PSA^d^	*	*			*	*	*	*
RT^d^and brachytherapy dose				*				

^a^assessments performed after complete treatment

^b^screening procedures carried out as per standard of care

^c^start day of second treatment modality

^d^Quality of life (QoL), International Prostate Symptom Score (IPSS), International Index of Erectile Function Scale (IIEFS), Functional Assessment of Cancer Therapy-Prostate (FACT-P), Common Terminology Criteria for Adverse Events (CTCAE), androgen deprivation therapy (ADT), prostate-specific antigen (PSA), radiotherapy (RT).

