## Discussion

If the results from this feasibility trial show evidence that the sequence of treatment modality does affect the patients’ toxicity profiles, then funding would be sought to conduct a large, multicenter, randomized controlled trial.

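### The trigger for a further trial names no endpoint, every secondary comparison is tested at an unadjusted 5%, and the primary test can hardly supply the significant difference

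*Protocol article*

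**What the plan says.** All references are to the protocol article.

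- **Endpoints** (Primary and Secondary Endpoints). The primary endpoint is grade 3 genitourinary (GU) toxicity. GU grades 1 and 2, gastrointestinal (GI) grades 1 to 4, PSA recurrence-free survival, overall survival and quality of life are secondary.
- **Significance level** (Statistical Analysis). "All statistical significance testing will be at the 5% significance level". No adjustment, testing order or exploratory status accompanies this.
- **Symptom scores** (Secondary Endpoint Efficacy Analysis, repeated in Statistical Analysis). "For the IPSS and IIEFS scale scores, the two means at each of the follow-up assessments will be compared using a two-sided permutation" (that is, a permutation t test). The same scores also enter a "repeated measures analysis of variance on the four follow-up scores", described as an assessment of trends, with baseline as covariate.
- **Toxicity percentages** (Statistical Analysis). "For categorical data based on adverse events, percentages will be compared using Fisher’s exact test". A log-rank test covers PSA relapse-free survival.
- **What follows the trial.** Rationale and Risks/Benefits: "Provided a significant difference between the two treatment arms is achieved following final analysis", the result will be considered as input to a pivotal study. Discussion, and in the same terms the Abstract's Conclusions: "If the results from this feasibility trial show evidence that the sequence of treatment modality does affect the" toxicity profiles of patients, funding for a large multicenter trial would be sought. No endpoint is named in any of these places.
- **Toxicity tools** (Trial Design). IPSS, IIEFS and FACT-P are listed with CTCAE as tools for assessing toxicity.
- **Size** (Sample Size). There are 25 patients per arm, a number chosen to evaluate processes, patient experience and adherence rather than on statistical grounds.

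**The concern.** The condition for a further trial is worded so that a significant result on any toxicity measure could be held to satisfy it. IPSS and IIEFS are listed as toxicity tools, so a P value below .05 on one scale at one visit fits the wording as well as a result on grade 3 GU toxicity does.

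This matters because both arms receive the same two treatments in a different order, so no difference in toxicity is a realistic truth. If the primary test can hardly reach significance while many secondary tests each run at 5%, the decision falls by default to the secondary tests. At stake is whether a large trial is proposed, and a sequence effect reported, on what may be a chance finding.

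**Working it through.** The document states no family-wise error rate and no power, so there is no figure of its own to reproduce.

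**Step 1. Can the primary test supply the significant difference?** Inputs: 25 per arm (Sample Size) and a grade 3 GU rate of 1.6% (Rationale and Risks/Benefits). Expected events in the whole trial are 50 × 0.016 = 0.8. For r events in one arm and none in the other, the two-sided Fisher P is 2 × C(25, r) / C(50, r):

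- r = 5: 2 × 53,130 / 2,118,760 = .0502
- r = 6: 2 × 177,100 / 15,890,700 = .022

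At least 6 against 0 is therefore needed. With 1.6% in both arms, exact enumeration gives a probability of P<.05 of about 0.0003%.

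**Step 2. How many other tests are there?** The text speaks of four follow-up scores, which gives 2 scales × 4 = 8 score t tests. The schedule table, as it can be read here, marks these questionnaires after treatment at 3, 9 and 12 months only, which gives 2 × 3 = 6. Both counts are carried forward. If each grade is tested separately there are seven Fisher tests (the primary plus six secondary grades). The repeated-measures tests and one log-rank test come on top.

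**Step 3. Independent tests as a reference.** 1 − 0.95^k gives 26.5% for k = 6 and 33.7% for k = 8. Scores over time are correlated, which lowers these figures.

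**Step 4. Fisher tests add little.** At 25 per arm their true size is about 0.2% at a 6.5% rate, 2.2% at 20%, 2.3% at 30% and 2.8% at 62%. Taken as independent, all seven together add 1 − (0.9978 × 0.9778 × 0.9771 × 0.9718) ≈ 7.4%; the three rarest grades contribute almost nothing.

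**Step 5. Simulation under no effect.** 10,000 trials per scenario, 25 per arm.

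- From the document: rates of 1.6% (GU grade 3), 62% (GU grade 2) and 6.5% (GI grade 2).
- Assumed: 30% (GU grade 1), 20% (GI grade 1), 0.5% (GI grade 3), 0.1% (GI grade 4); correlation 0.3 to 0.85 within a scale and 0 to 0.2 between scales.
- Simplifications: ordinary t tests in place of permutation t tests; no baseline adjustment; repeated measures represented by a mean-over-visits and a linear-trend contrast; Fisher and log-rank tests independent of the scores, with log-rank at 5%.

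Chance of at least one P<.05:

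| Tests counted | 3 visits | 4 visits |
|---|---|---|
| Score t tests only | 17–26% | 20–32% |
| plus seven Fisher tests | 23–31% | 26–37% |
| plus repeated measures | 30–36% | 32–41% |
| plus log-rank | 34–40% | 36–45% |

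At within-scale correlations of 0.5 to 0.7, the second row narrows to 26–30% and 30–34%. With three Fisher tests instead of seven, the score and Fisher tests together give 21–31%.

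**The case against.** The strongest reply is that this is a feasibility study. Its size has no statistical basis, the analysis is described as an attempt to follow main-study methods, and a false positive leads only to another randomized trial that would test the finding. Error control across secondary outcomes is not normally demanded in that setting, and details may sit in an analysis plan that is not shown. Most of this stands: it limits the severity and removes any need for formal adjustment. It does not remove the point, which rests on two things the article does state: a 5% level for every test, and a progression condition that rests on significance and names no endpoint.

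Four stronger readings are tempting, and the document does not support them.

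- A reader might infer that there is no hierarchy at all. There is one: a single primary endpoint ranked above the secondaries. What is missing is an order or status among the secondary comparisons, and a link from the progression condition to the primary.
- A reader might infer that any single P<.05 establishes the trial's conclusion. The text says only that a result would be considered, or funding sought. It leaves that use open but does not prescribe it.
- A reader might compare the simulated rate with a promised 5%. The 5% is a per-test level; no family-wise rate is promised.
- A reader might say that the visit tests and the repeated-measures analysis compete for the same conclusion. The latter is described as assessing trends, which is a different question. The plan simply does not say which between-arm contrast counts for each scale.

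The statement about the primary test also depends on the rate. If one arm had 1.6% and the other 20% or 26%, its power would be about 32% or 59%. A large true excess could therefore be detected, but a result close to the quoted rate in both arms could not be significant.

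**Conclusion.** The point holds in a limited form. The progression condition is separate from the primary endpoint, and at the stated 1.6% rate a significant difference would in practice come from secondary tests run at an unadjusted 5%. With no true effect, the chance of at least one such result is roughly 20–35%. The full range is about 17–45%. It depends on the assumed correlations and grade rates, on three or four visits, and on whether the repeated-measures and log-rank tests are counted. No single figure can be derived from the document. Because the consequence is a further trial rather than a change of practice, this is a worthwhile and inexpensive improvement, not a flaw that invalidates the design.

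**What to change.** 1. In Secondary Endpoint Efficacy Analysis and Statistical Analysis, label all secondary between-arm comparisons exploratory. Report them as estimates with the bootstrap and Newcombe 95% limits that are already planned.
2. For IPSS and IIEFS, prespecify one between-arm contrast per scale and treat the visit-by-visit tests as descriptive.
3. In the Abstract's Conclusions, Rationale and Risks/Benefits, and the Discussion, state that one nominal P<.05 on a secondary test is not by itself evidence of a sequence effect, nor the trigger for a further trial.

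A Holm adjustment is optional and not required in a feasibility study. Confining significance testing to grade 3 GU toxicity would not be a full answer either, because that test is nearly inert at the quoted rate; the useful change is in how secondary results are labelled and used.

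The cost is wording only, with no added patients, visits or data. The downside is that fewer secondary results can be called significant.

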#### Baseline Procedures

The following baseline procedures will be performed: physical examination, measurement of vital signs, and assessment of QoL baseline (IPSS, IIEFS, FACT-P, CTCAE questionnaires), hematology, biochemistry, concomitant treatment (eg, androgen deprivation therapy [ADT]), and PSA.

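### The visit-by-visit IPSS and IIEFS comparisons leave out the baseline score already collected; a baseline-adjusted mixed model would gain precision at no data cost and cope better with missed visits

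*Protocol article*

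**What the plan says.** The protocol article describes the analysis of IPSS and IIEFS under Secondary Endpoint Efficacy Analysis and again, in more detail, under Statistical Analysis. It has two parts.

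- **Arm comparison at each visit.** The test is stated as follows: "the two means at each of the follow-up assessments will be compared using a two-sided permutation" version of the t test. The interval has its own statement, which under Statistical Analysis reads: "the 95% confidence limits for the difference between the means will be calculated using a bootstrap method using 9999 resamplings". No baseline term is mentioned for either.
- **Trend over time.** A "repeated measures analysis of variance on the four follow-up scores with the baseline score as a covariate".

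The baseline scores exist: Baseline Procedures lists "assessment of QoL baseline (IPSS, IIEFS, FACT-P, CTCAE questionnaires", and Table 2 marks these questionnaires at baseline and then at 3, 9 and 12 months after treatment.

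Three further statements bear on the point. On the analysis set: "All randomized participants will be included in the analyses". On feasibility of the planned methods: "this might not always be possible depending on the pattern of the outcomes and missing values". On size: "two samples of 25 patients—50 overall—will be randomized to the two treatments". R is named as the software, without a function or a missing-data option.

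**The concern.** The estimate and confidence interval that a reader will look at for each visit come from the raw follow-up means. The covariate most likely to explain variation in a symptom score, the man's own starting value, is on file and used one sentence later, but only for the trend.

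In a trial this small, chance can leave the arms unequal at baseline. The Randomization section describes a simple 1:1 scheme and refers to stratification factors without naming them, so nothing shown balances baseline symptom scores by design. An unadjusted difference is then less precise than it could be and picks up part of any starting gap.

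The trend analysis has a different weakness. Repeated measures ANOVA in its usual form needs every visit for every patient. If it is run that way, one missed questionnaire removes the man, and the statement that all randomized participants are included would not hold for that analysis. The protocol foresees that missing values may get in the way but names no alternative.

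**Working it through.** **Inputs from the protocol.** 25 per arm, 50 in total (Sample Size). Two-sided permutation test, 5% level (Statistical Analysis). Four follow-up scores in the text of Statistical Analysis; three post-treatment IPSS/IIEFS assessments in Table 2. The plan's own figure, 2 × 25 = 50, is consistent, but Sample Size says it was not set on statistical grounds, so there is no power calculation to reproduce.

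**Assumptions, because the protocol gives no figure.** Baseline-to-follow-up correlation r of 0.3 to 0.7. Missed questionnaires at 10% per visit, with 5% and 20% as the range. The 10% dropout figure in the protocol concerns screen failures and cannot be used here.

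**Step 1: precision.** Baseline adjustment multiplies the standard error by √(1 − r²). The sample size with the same precision unadjusted is 25/(1 − r²) per arm. The difference detectable with 80% power, in SD units by normal approximation, is (1.960 + 0.842) × √(2/25) × √(1 − r²), which is 0.79 with no adjustment.

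| r | √(1 − r²) | SE cut | Equivalent n per arm | Detectable difference | Power for 0.5 SD |
|---|---|---|---|---|---|
| no adjustment | 1 | – | 25 | 0.79 SD | 42% |
| 0.3 | 0.954 | 5% | 27.5 | 0.76 SD | 46% |
| 0.5 | 0.866 | 13% | 33.3 | 0.69 SD | 53% |
| 0.7 | 0.714 | 29% | 49.0 | 0.57 SD | 70% |

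**Step 2: chance imbalance.** The standard error of the baseline difference is √(2/25) = 0.283 SD. A gap of more than 0.3 SD in either direction therefore has a chance of 2 × [1 − Φ(0.3/0.283)] = 29%; a gap of more than 0.5 SD has a chance of 8%. With equal SDs, the raw follow-up difference carries r times the gap. A 0.3 SD gap shifts it by 0.09, 0.15 or 0.21 SD at r = 0.3, 0.5 or 0.7.

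**Step 3: men kept if the trend analysis uses only complete records.** With independent misses at rate m over k visits, the expected number is 50 × (1 − m)^k.

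| m per visit | four scores | three scores |
|---|---|---|
| 5% | 40.7 | 42.9 |
| 10% | 32.8 | 36.5 |
| 20% | 20.5 | 25.6 |

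Independence is the unfavourable case. If the same 10% of men miss every visit, 50 × 0.90 = 45 are kept, whichever number of visits applies. At 10% the result thus lies between about 33 and 45 with four scores, and between about 36 and 45 with three.

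**The case against.** The strongest reply is that nothing here is invalid. A permutation test on randomized arms holds its 5% level without adjustment, and the plan does use baseline, in the longitudinal analysis. Pairing simple visit-wise tests with a baseline-adjusted model is defensible in a feasibility study whose size was never set for power and whose primary endpoint is something else. All of that stands. It limits the point to efficiency and robustness, but it is no reason to leave a measured covariate out of the main arm comparison.

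Three stronger readings are tempting, and the documents do not support them.

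- **That the ANOVA drops patients and so contradicts the all-randomized statement.** The protocol states no deletion rule and names no R routine. Listwise deletion belongs to the classical form of the method, and some routines accept incomplete records. The protocol also warns openly that missing values may prevent the planned analysis, and Participant Withdrawal keeps men who stop treatment in follow-up to one year. This is a tension, not a proven contradiction.
- **That baseline imbalance passes in full into the estimate.** Only about r times the gap does, and averaged over randomizations the unadjusted estimate is unbiased.
- **That sicker men will be lost and the trend biased.** The protocol contains no information on who misses questionnaires.

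The proposed model has limits too. It cannot use a man with no follow-up score, and it relies on scores being missing at random.

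**Conclusion.** The point holds as a free improvement. The visit-wise IPSS and IIEFS comparisons and their bootstrap limits are unadjusted, although the baseline score is available. At assumed correlations of 0.3, 0.5 and 0.7, adjustment would cut the standard error by 5%, 13% and 29% and would remove the part of a chance baseline gap that now enters the estimate.

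The missing-visit part is conditional. If the repeated measures ANOVA is run in its usual form, and if 10% of questionnaires are missed per visit, between about 33 and 45 of 50 men would be kept with four scores, depending on how far the misses fall on the same men. The correlations, the missed-visit rate and its pattern are all assumptions.

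The consequence is modest, since these are secondary analyses in a 50-patient feasibility trial. It is still worth correcting, because Statistical Analysis says the data will be treated as they would be in a main study, so the choice may be carried forward.

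**What to change.** 1. Make the arm difference at each visit, and its 95% interval, baseline-adjusted. The preferred route is one linear mixed model per scale with arm, visit, arm-by-visit interaction and baseline score, fitted to all available follow-up scores. The visit contrasts replace the raw comparisons, and the same model serves for the trend.
2. If permutation inference is wanted, permute the arm labels and use the adjusted contrast as the test statistic.
3. For these scales, define the analysis set as all randomized patients with at least one follow-up score, analysed in their allocated arm, and state the missing-at-random assumption.
4. Reconcile the four follow-up scores in the text with the three post-treatment IPSS/IIEFS assessments in Table 2 (3, 9 and 12 months).

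The cost is a few sentences in the analysis plan and a few lines of R. Steps 1 to 3 need no new data; step 4 needs only that the text and the schedule agree.
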